### 1. Background

Contaminated drinking water is a leading cause of morbidity and mortality in low-income settings. Safe drinking water is of particular concern for HIV-positive mothers since many HIV-infected Zambian women choose replacement feeding and early cessation of breastfeeding of infants to minimize the risk of transmission of the virus (CIGNIS study results; S Filteau, L Kasonka et al., submitted). In resource-poor settings, HIV-positive mothers must choose between breastfeeding their infant and potentially transmitting HIV, or formula feeding their infant and thereby risking diarrhoeal disease morbidity and mortality. However, the extent to which the drinking water actually being used by this population is safe, and what steps could be taken to ensure the microbiological quality of such water, is largely unknown.

Our previous work in Zambia found that HIV-positive mothers with children <2 years would potentially benefit from an intervention that encourages HIV-positive mothers to treat their water at the household level before using it for their young children and all household members. In a cross-sectional study of 254 households, we found that 26% of children <2 years had diarrhoea in the past week, 53% of children <2 years received supplemental water in the past 2 days, and 70% of households had faecally contaminated drinking water. This proposed study aims to assess a household water treatment technology in the form of a randomized controlled, trial.

**2. Objectives**

This randomized, controlled trial (RCT) pilots a household water treatment and safe storage (HWTS) technology, the LifeStraw Family filter. This research aims to answer the following question:

*Would children <2 years and other members of households in which HIV-positive mothers are providing replacement and complementary feeding potentially benefit from the use of a filter designed to eliminate microbial pathogens from drinking water at the household level?*

The specific objectives of the pilot study are:

- To examine the use, longevity and acceptability of LifeStraw Family, both for children <2 years and for drinking water by all household members
- To examine the microbiological performance of LifeStraw Family, measured in terms of thermotolerantcoliforms (TTC), a well-established WHO indicator organism for faecal contamination (WHO 2004)
- To assess the impact of the intervention on the longitudinal prevalence of diarrhoea among children < 2 years and all household members, measured both as reported by the primary caretaker of the child and by their weight-for-age z-score (WAZ)—a proxy for diarrhoea (Schmidt, Boisson et al. 2009).

**3. Sample Size**

One hundred and twenty households will be followed for one year. The sample size of one-hundred households is based on the primary outcome (adoption) and is based on an estimated 60% of the study population satisfying the conditions for use, with a standard of 0.05, for a 95% confidence interval of 50-70%. An additional 20 households of HIV-negative mothers will be included to reduce stigma of the study. The study population will be followed for one year to account for seasonal variability in water quality.

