**5. Study Population and Recruitment**

Study participants will be recruited through the community health clinic for the catchment area or areas. In our cross-sectional study, it was particularly efficient to recruit through ART programs, nutrition programs, and the under-five clinics at the community health centres; depending on the health centre(s) chosen, we may use similar recruitment methods. Women will be eligible to participate in the study if (i) they report that they are HIV-positive based on clinical testing, (ii) they currently have a child age six months to one year at the beginning of the study, and (iii) they reside in a household located in the designated peri-urban area(s) in or around Lusaka, Zambia, (vi) drinking water of poor quality. HIV-status of mothers will be confirmed by the child’s exposure status (‘exposed’ or ‘unexposed’) on the child’s health record. Women that are interested in participating will be asked for consent and household location information will be obtained for follow-up. It is possible that some of the same HIV-positive mothers from our cross-sectional study will be included in the RCT. In order to reduce stigma, we plan to include an additional 20 HIV-negative mothers (10 in intervention group and 10 in control). These mothers will also be recruited from the selected community health clinic(s). We will be asking about infant HIV-status if known, though this will not be required for participation. Participating mothers will be reminded that HIV-testing of children is available in Zambia free-of-cost, including PCR testing from 6 weeks. If mothers subsequently choose to have their children undergo HIV testing, we will ask that they contact us with the results.

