### 6. Baseline Survey and Intervention

*Baseline survey and randomization*

Before the water filter is distributed, a baseline survey will be conducted of the recruited participants. The baseline study will include information on demographics, sanitation facilities, hygiene practices, water sources and treatment practices and other factors that could potentially impact the outcomes of interest. After the baseline survey, the intervention will be randomly allocated to half of the recruited participants. Participating households will be numbered consecutively and then allocated into the two groups using a random number generator. Households that do not receive the filter at the beginning of the study will receive the filter at the end of the study. Households will receive training on how to use and maintain the filter prior to receiving the intervention.

*The Intervention*

The intervention consists of the Lifestraw Family filter for household water treatment and a storage container to encourage safe water storage of treated water. The LifeStraw Family is a HWTS filtration technology shown to remove microbial contamination from drinking water and to be acceptable to users. The device was chosen because it has been shown to be effective against the full array of microbial pathogens and to have a longevity that exceeds one year (Clasen, Naranjo et al. 2009). Developed by Vestergaard Fransen SA, LifeStraw Family is a new household-based gravity filter system that uses ultrafiltration mechanisms to remove pathogens. The filtration unit consists of a hollow-fibre cartridge of 20 nm diameter pore size. Untreated water is poured into a 2.5L container, flows down a 1m long tube designed to provide head pressure, and through the ultrafiltration cartridge where it is dispensed via tap. The cartridge is also equipped with a backwash inlet to facilitate cleaning of the cartridge, thus minimizing clogging and improving longevity. The flow rate of the device averages at 8.8L/hour (over design life of 18,000L with periodic cleaning and backwashing),(Clasen, Naranjo et al. 2009) and the flow shuts down when the hollow-fibres are exhausted, indicating when to replace the cartridge.

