**7. Research Methods and Outcomes**

Each of the 120 households will be visited monthly for water quality testing and household questionnaires. Specifically, the research methods will include:

- Household surveys, observations, and focus group discussions to evaluate use, longevity, and acceptability (objective 1)
- Routine water quality testing of source, treated, and stored water to evaluate microbiological performance (objective 2)
- Regular disease surveillance, including household visits to assess reported diarrhoea, changes in weight and hospital admissions for diarrhoea (objective 3)

*Use, Longevity and Acceptability*

Previous research has suggested that a principal reason for failure to achieve the potential health gains from HWTS interventions is sub-optimal adoption—particularly exclusive use by the most vulnerable segments of the population. In this RCT, use will be the principal outcome. Each filter unit will be encoded with a number and the date distributed will be recorded. The investigator will develop criteria for assessing use and a set of indicators based thereon (e.g., filter mounted for use in the household, filter reported to have been used on the day of the visit or the previous day, storage vessel contains water that is reported to have been treated, and microbiological quality of water is at least 1 log lower in TTC than source water). Thereafter, the investigator will determine whether the device is in use during each household visit using the specified indicators that combine reporting and observations. Furthermore, approximately 10% of the filters will include flow meters that record the quantity of water that has been run through the filter to objectively measure filter use. If the device is not being used at all, the investigator will record the reasons according to the mother. If the device is no longer in use due to clogging, the investigator will record the date it clogged and attempt to restore use by normal cleaning. If service cannot be restored, the investigator will replace the cartridge or other failed component and note the change.

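### Section 3's 95% interval of 50-70% for filter use assumes about 100 households with a filter; the 1:1 allocation supplies about 50 to 60, so the expected interval is about 46-74% or 48-72%

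*Protocol*

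**What the plan says.** Section 3 ties the size of the trial to one outcome: "The sample size of one-hundred households is based on the primary outcome (adoption"). Section 7 confirms the choice: "In this RCT, use will be the principal outcome". The planning values are "an estimated 60% of the study population satisfying the conditions for use, with a standard of 0.05, for a 95% confidence interval of 50-70" percent. The word error appears to be missing after standard; the arithmetic below supports that reading.

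Section 3 also gives the total, "One hundred and twenty households will be followed for one year", made up of the 100 households plus 20 with HIV-negative mothers, who are added to reduce stigma. Section 5 splits those 20 evenly: "an additional 20 HIV-negative mothers (10 in intervention group and 10 in control").

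Section 6 sets the allocation: "the intervention will be randomly allocated to half of the recruited participants". It then says when the others are served: "Households that do not receive the filter at the beginning of the study will receive the filter at the end of the study".

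The example indicators of use in Section 7 include a filter set up in the home and its reported use on the day of the visit or the day before. The first endpoint for Objective 1 in Section 8 is the percentage of households that use the filter throughout the study, so each household counts once.

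**The concern.** The sample size calculation and the allocation use different denominators. Section 3 treats all 100 households as able to show use. Under Section 6, only those allocated a filter at the start can do so during follow-up. A control household has no device to mount or use, and by the time it receives one the observation period is over.

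At stake is the protocol's only numerical justification of its size. Ethics committees and readers are told to expect the primary estimate to within about 10 percentage points, and the design as written does not deliver that.

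**Working it through.** **Inputs**
- Expected use p = 0.60, SE 0.05, target interval 50-70% (Section 3).
- 120 households: 100 with HIV-positive mothers and 20 with HIV-negative mothers (Sections 3 and 5).
- Filter to half; controls served at the end (Section 6). HIV-negative households split 10 and 10 (Section 5).

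**Formulas.** SE = √(p(1 − p)/n); 95% interval = p ± 1.96 × SE. With p = 0.60, p(1 − p) = 0.24.

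**Step 1: reproduce the stated figure.**
- n = 100: SE = √(0.24/100) = 0.049; 1.96 × 0.049 = 0.096; interval 50.4-69.6%, which rounds to the stated 50-70%.
- Solving for SE = 0.05: n = 0.24/0.05² = 96.
- Solving for a half-width of 0.10: n = 1.96² × 0.24/0.10² = 92.2, so 93.

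The arithmetic in Section 3 is therefore sound for roughly 93 to 100 households that can be assessed for use.

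**Step 2: count the households that can be assessed.**
- All households with a filter: 120/2 = 60.
- HIV-positive households with a filter: 60 − 10 = 50.

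**Step 3: check that 60% cannot refer to both arms together.** If controls counted as non-users, complete use in the filter arm would give 50/100 = 50% (or 60/120 = 50%). An expected 60% would then be unattainable, so the planning value makes sense only within the filter arm.

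**Step 4: recompute for the filter arm.**

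| Households with a filter | SE | 95% interval | Half-width | Exact (Clopper-Pearson) |
| --- | --- | --- | --- | --- |
| 100 (as assumed in Section 3) | 0.049 | 50.4-69.6% | 9.6 points | 49.7-69.7% |
| 60 | 0.063 | 47.6-72.4% | 12.4 points | 46.5-72.4% |
| 50 | 0.069 | 46.4-73.6% | 13.6 points | 45.2-73.6% |

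The full width is 24.8 or 27.2 points, against the 20 stated.

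**Step 5: loss to follow-up.** Section 3 states no allowance. As an assumption only, a loss of 10% to 20% from 50 households leaves 45 to 40. With n = 45, 1.96 × √(0.24/45) = 0.143, giving 45.7-74.3%. With n = 40, 1.96 × √(0.24/40) = 0.152, giving 44.8-75.2%.

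**The case against.** The strongest reply is that this is a pilot reporting a descriptive percentage. No test, error rate or between-arm comparison depends on the interval, nothing is biased, and the half-width grows by only about 2 to 4 points over the stated 10. That stands, and it limits the weight of the point. It does not make the stated interval right.

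A second reply is that 12 monthly visits per household supply more information than 50 or 60 single observations. The calculation in Section 3 counts households, and the Section 8 endpoint gives one value per household over the whole study. A proportion of visits would be a different quantity, to which the 60% would not carry over. Its precision would also depend on a within-household correlation that the protocol does not give. Repeat visits therefore do not rescue the stated figure.

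A third concerns the denominator. Section 3 builds its 100 on the HIV-positive group, which points to 50. Section 8 does not restrict the endpoint by HIV status and Section 7 has all 120 households visited, which points to 60. Both readings are fair, and neither reaches 93.

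A reader might go further and infer that, because the recomputed interval covers 50%, the trial could no longer conclude that most households adopt the filter. The protocol does not support that. It sets no 50% threshold and no decision rule for adoption. The interval it states already touches 50%, and the exact interval with 100 households (49.7-69.7%) includes it too, so the smaller denominator does not create that feature.

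**Conclusion.** The point holds. Nothing in the protocol makes 100 households available for the use outcome. If 60% use is observed, the 95% interval to expect is about 46-74% with 50 households or 48-72% with 60, in place of 50-70%. It would be wider still with any loss to follow-up.

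This rests on three readings: that the 0.05 is a standard error, that use can be observed only in households holding a filter during follow-up, and that the household is the unit, as Sections 3 and 8 both have it. The consequence is a moderate loss of precision in a descriptive estimate. Validity is untouched, and the randomised comparisons under Objective 3 are not affected by this point.

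**What to change.** Restate the precision in Section 3 for the filter arm and name the denominator. Suggested wording, with one alternative kept: Use will be assessed in the households allocated the filter at the start of the study. If 60% meet the conditions for use, the 95% confidence interval will be about 46-74% (50 HIV-positive households, standard error 0.069) or 48-72% (all 60 households with a filter, standard error 0.063), before loss to follow-up. The same denominator should then be named for the Objective 1 endpoint in Section 8.

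The cost is a change of wording and a less favourable figure; conduct and data collection stay as they are. If the sponsor needs the interval of 50-70% itself, the filter arm would have to hold about 93 to 100 households. At 1:1 that is 2 × 93 = 186 to 2 × 100 = 200 in total, plus any HIV-negative households if these are not counted in the denominator. That is a much larger study, and correcting the statement does not require it.

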**4. Location**

The site(s) will be in or around Lusaka, Zambia and should meet the following criteria:

- Sufficient number of households with children <2 years born to HIV-positive mothers who know (or willing to be tested) and are willing to disclose their HIV status for purposes of this study
- Available testing, care, and counselling for HIV-positive individuals
- Active health clinic with staff that can help with the recruitment process, through ART programs, nutrition programs, under-five clinics, etc
- Population relying on unsafe drinking water, characterized by unimproved water supplies and thermotolerant coliform (TTC) contamination, as measured in CFUs/100 mL
- Majority of households are not treating their water in some microbiologically effective manner (e.g., boiling)
- The population has sufficient quantity and access to water supplies, so that major water deficiency is microbiological quality
- The population and community leaders desire to participate in the study

**5. Study Population and Recruitment**

Study participants will be recruited through the community health clinic for the catchment area or areas. In our cross-sectional study, it was particularly efficient to recruit through ART programs, nutrition programs, and the under-five clinics at the community health centres; depending on the health centre(s) chosen, we may use similar recruitment methods. Women will be eligible to participate in the study if (i) they report that they are HIV-positive based on clinical testing, (ii) they currently have a child age six months to one year at the beginning of the study, and (iii) they reside in a household located in the designated peri-urban area(s) in or around Lusaka, Zambia, (vi) drinking water of poor quality. HIV-status of mothers will be confirmed by the child’s exposure status (‘exposed’ or ‘unexposed’) on the child’s health record. Women that are interested in participating will be asked for consent and household location information will be obtained for follow-up. It is possible that some of the same HIV-positive mothers from our cross-sectional study will be included in the RCT. In order to reduce stigma, we plan to include an additional 20 HIV-negative mothers (10 in intervention group and 10 in control). These mothers will also be recruited from the selected community health clinic(s). We will be asking about infant HIV-status if known, though this will not be required for participation. Participating mothers will be reminded that HIV-testing of children is available in Zambia free-of-cost, including PCR testing from 6 weeks. If mothers subsequently choose to have their children undergo HIV testing, we will ask that they contact us with the results.

### 6. Baseline Survey and Intervention

*Baseline survey and randomization*

Before the water filter is distributed, a baseline survey will be conducted of the recruited participants. The baseline study will include information on demographics, sanitation facilities, hygiene practices, water sources and treatment practices and other factors that could potentially impact the outcomes of interest. After the baseline survey, the intervention will be randomly allocated to half of the recruited participants. Participating households will be numbered consecutively and then allocated into the two groups using a random number generator. Households that do not receive the filter at the beginning of the study will receive the filter at the end of the study. Households will receive training on how to use and maintain the filter prior to receiving the intervention.

*The Intervention*

The intervention consists of the Lifestraw Family filter for household water treatment and a storage container to encourage safe water storage of treated water. The LifeStraw Family is a HWTS filtration technology shown to remove microbial contamination from drinking water and to be acceptable to users. The device was chosen because it has been shown to be effective against the full array of microbial pathogens and to have a longevity that exceeds one year (Clasen, Naranjo et al. 2009). Developed by Vestergaard Fransen SA, LifeStraw Family is a new household-based gravity filter system that uses ultrafiltration mechanisms to remove pathogens. The filtration unit consists of a hollow-fibre cartridge of 20 nm diameter pore size. Untreated water is poured into a 2.5L container, flows down a 1m long tube designed to provide head pressure, and through the ultrafiltration cartridge where it is dispensed via tap. The cartridge is also equipped with a backwash inlet to facilitate cleaning of the cartridge, thus minimizing clogging and improving longevity. The flow rate of the device averages at 8.8L/hour (over design life of 18,000L with periodic cleaning and backwashing),(Clasen, Naranjo et al. 2009) and the flow shuts down when the hollow-fibres are exhausted, indicating when to replace the cartridge.

Independent laboratory testing of the filter has demonstrated high microbiological performance on the full array of waterborne microbes. Through 20,000L (111% of design life) at moderate turbidity (15 NTU), the technology achieved log10 reduction values of 6.9 for *E. Coli*, 4.7 for MS2 coliphage (proxy for enteric pathogenic viruses), and 3.6 for *Cryptosporidium* oocysts (Clasen, Naranjo et al. 2009). Testing confirmed that the device meets the highest international standards for microbiological water purifiers. The device has the advantage (compared to chlorination technologies) of removing protozoan cysts such as *Cryptosporidium* oocysts, which are particularly prevalent in malnourished or HIV-positive infants in Africa (Mor and Tzipori 2008). It also removes viruses, a major challenge for most gravity-based filter medium, such as ceramics. Since the device is relatively easy to use, improves the appearance of water and does not rely on chemicals that adversely impact taste, adoption and use are likely to be greater than other HWTS products. Moreover, with a 20,000L design life, the unit can provide protection for an entire household for up to four years, minimizing supply chain challenges that present obstacles for consumable water treatment products.

The intervention will also include a vessel for safely storing water following treatment. Previous fieldwork with the LifeStraw Family filter has suggested that exclusive use of water treated with the filter is less then optimal, especially among young children, because of the inability to safely store and conveniently access water after treatment. The storage device will be procured locally and piloted to ensure acceptability by the study population. At a minimum, it will contain an opening that is too small to permit the entry of hands, and will allow drawing of water only via a tap or by pouring.

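### The allocation procedure as written does not deliver the stated 10/10 split of HIV-negative households; it should be run within maternal HIV status

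*Protocol*

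**What the plan says.** Three parts of the protocol bear on this.

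- **Section 3 (Sample Size)** sets the total: "One hundred and twenty households will be followed for one year". The precision argument rests on 100 of these. The others are extra: "An additional 20 households of HIV-negative mothers will be included to reduce stigma of the study".
- **Section 5 (Study Population and Recruitment)** states how the extra households fall between the arms: "we plan to include an additional 20 HIV-negative mothers (10 in intervention group and 10 in control". Maternal HIV status is reported at recruitment and confirmed from the exposure status on the child's health record.
- **Section 6 (Baseline Survey and Intervention)** gives the allocation. After the baseline survey, "the intervention will be randomly allocated to half of the recruited participants". The mechanism is: "Participating households will be numbered consecutively and then allocated into the two groups using a random number generator".

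No section mentions stratification, blocking or a separate list by maternal HIV status. Section 8 plans a multivariable model for the arm comparison, adjusted for potential confounders. It names age and socioeconomic status as examples and leaves the list open.

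**The concern.** Section 5 states a property of the allocation as fixed, and Section 6 describes a procedure that achieves it only on average. With half of 120 households in each arm, 10 HIV-negative households per arm also implies 50 HIV-positive households per arm. A single random split of one list guarantees neither number.

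Maternal HIV status is plausibly prognostic on the protocol's own account. Section 1 links maternal HIV to replacement feeding and early weaning, and formula feeding to diarrhoeal risk. Section 6 notes that *Cryptosporidium* is especially common in malnourished or HIV-positive infants. Section 7 says that feeding practices may affect diarrhoea prevalence. An uneven split would therefore add avoidable noise to the Objective 3 comparisons of diarrhoea and weight-for-age between two arms of about 60 households. It would also leave the trial reporting group sizes other than those planned.

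**Working it through.** **Inputs**

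- N = 120 households in total (Section 3).
- K = 20 HIV-negative households, leaving 100 HIV-positive (Sections 3 and 5).
- n = 60 households allocated to the filter, half of 120 (Section 6).
- Stated split: 10 and 10 (Section 5).

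**Step 1. The stated figure as an average.** Let X be the number of HIV-negative households in the filter arm. If 60 of 120 are drawn at random from one list, X is hypergeometric with mean n × K/N = 60 × 20/120 = 10. The stated split is therefore the expected value.

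**Step 2. The spread around it.** Variance = n × (K/N) × (1 − K/N) × (N − n)/(N − 1) = 60 × (20/120) × (100/120) × (60/119) = 4.20, so the SD is 2.05.

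**Step 3. How often the stated split occurs.** P(X = 10) = C(20,10) × C(100,50) / C(120,60) = 0.193. Summing both tails:

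| Split of the 20 | Probability, 60 of 120 drawn | Probability, independent coin flip |
|---|---|---|
| exactly 10/10 | 19.3% | 17.6% |
| any other split | 80.7% | 82.4% |
| 8/12 or worse | 46.3% | 50.3% |
| 7/13 or worse | 22.0% | 26.3% |
| 6/14 or worse | 8.5% | 11.5% |
| 5/15 or worse | 2.6% | 4.1% |

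The last column, Binomial(20, 0.5), covers the reading in which the generator decides each household independently. Under that reading even an overall 60/60 split occurs only 7.3% of the time, so the first column is the reading kinder to the protocol.

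**Step 4. Effect on precision for filter use.** The central 95% range of X is 6 to 14, so the filter arm holds between 54 and 46 HIV-positive households. With the 60% use assumed in Section 3, the 95% half-width is 1.96 × √(0.6 × 0.4/m):

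- m = 54: 13.1 points
- m = 50: 13.6 points
- m = 46: 14.2 points

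The allocation therefore moves the half-width by about half a point either way. (The 50–70% interval in Section 3 is reproduced with 100 households: SE 0.049, interval 50.4–69.6%. That calculation does not depend on the split.)

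**Step 5. Effect on an unadjusted arm comparison.** The protocol gives no outcome difference by maternal HIV status, so a difference of 10 to 20 points in risk is assumed here.

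- Split 6/14: HIV-negative shares are 6/60 = 10.0% and 14/60 = 23.3%, a gap of 13.3 points. Shift = 0.133 × 10 to 20 = 1.3 to 2.7 points.
- Split 8/12: shares are 13.3% and 20.0%, a gap of 6.7 points. Shift = 0.7 to 1.3 points.

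For scale, take the 26% one-week diarrhoea prevalence in Section 1 and 60 children per arm. The 95% half-width of a difference at one visit is 1.96 × √(2 × 0.26 × 0.74/60) = 0.157, about 16 points. Repeated visits would narrow it.

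**Step 6. After the change.** Drawing exactly half within each stratum gives 10/10 and 50/50 with probability 1. The arms stay at 60/60 and the total at 120.

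**The case against.** The strongest reply is that the protocol never says the draw is unstratified. Section 5 can be read as the target and Section 6 as the random mechanism, run within HIV status. That may have been intended. It is not written, however: Section 6 describes one consecutive numbering of the participating households and nothing else. Allocation is also protocol content, and an analysis plan cannot restore a split once the draw is made. The reply shows that one clause would settle the matter; it does not remove the mismatch.

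Other objections do stand, and they limit what a reader might infer.

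- **That the trial would be biased or confounded.** A chance imbalance after valid randomisation is not bias. The open-ended adjustment in Section 8 can also include maternal HIV status, although it does not name it.
- **That the principal outcome is affected by arm imbalance.** Filter use is a proportion among households that have the filter, not a comparison of arms. The imbalance matters only for the Objective 3 comparisons, in a study that calls itself a pilot.
- **That the HIV-positive filter group becomes too small.** The protocol sets no minimum of 50. The number is as likely to exceed 50 as to fall short, and precision hardly changes.
- **That pooling the HIV-negative households distorts the adoption estimate.** If use differed by 20 points (assumed), pooling would shift the estimate by 10/60 × 20 = 3.3 points. That figure is computed at a perfect 10/10 split and would persist under stratified allocation, so it is no evidence about randomisation. The choice of analysis set is commonly left to a statistical analysis plan, which is not at hand.

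**Conclusion.** The point holds as an inconsistency between Sections 5 and 6. Followed as written, the allocation misses the stated 10/10 split in about 81% of draws and gives 7/13 or worse in 22%. This rests on reading Section 6 as one list of 120 with 60 drawn; independent coin flips would do slightly worse.

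The consequences are modest. Randomisation stays valid, and the half-width for filter use among HIV-positive households stays between 13.1 and 14.2 points over the central 95% of draws. An unadjusted Objective 3 contrast would shift by up to about 2.7 points at 6/14 if risk differed by 20 points by HIV status, which is an assumption. The documents do not support a claim of confounding or of material loss of precision. The change is worth making because a stated feature of the design would usually fail to occur, and because the imbalance can be avoided at no cost in sample size.

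**What to change.** Amend the randomisation paragraph in Section 6 to say that households are numbered and randomised separately within maternal HIV status, with exactly half of each stratum allocated to the filter: 50:50 among the 100 HIV-positive households and 10:10 among the 20 HIV-negative households. This brings it into line with Section 5.

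In Section 8, name maternal HIV status as a covariate in the models comparing intervention with control, so that the analysis reflects the stratified allocation.

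The cost is wording and a second randomisation list. The total stays at 120 and the arms at 60 each. No new data are needed, because HIV status is established at recruitment and allocation follows the baseline survey.
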